### Quality assurance and control

The research institutes will be monitored centrally and via on-site visits by a research nurse from Seoul National University Hospital who will follow the ICH-GCP guidelines. The trial institutes will also be visited regularly by the study coordinator and the study sponsor to ensure compliance with the study protocol and ICH-GCP guidelines. Complete source data verification will be performed by independent monitors. All the data collected during the trial will be stored in a secure electronic data capture system according to the ICH-GCP guidelines. A central study coordinator will coordinate the study. The Seoul National University Hospital will monitor the study’s progress and quality and the completeness of the study data.

### Access to data

The principal investigators and co-investigators will have access to the final trial dataset.

### Dissemination of data

The results of this study will be disseminated via professional journals and national, and international conferences. A lay summary of study results will be provided with ClinicalTrials.gov upon study completion.

### Protocol modifications

Major protocol modifications are not anticipated. If any important modifications occur, they will be notified through a modification request form to the Institutional Review Board of Seoul National University Hospital and communicated to all study personnel.

### Authorship

Authorship will be given to those who make considerable contributions to the study.

## Discussion

Our study is the first randomized controlled clinical trial on the efficacy of aspirin in patients with SEMS for malignant distal CBD obstruction. Endoscopic SEMS’ placement is currently regarded as the standard palliative treatment for patients with unresectable, malignant distal CBD obstruction. SEMS have a larger luminal diameter and guarantee longer patency than plastic stents, but their benefits in terms of survival have not been established despite several meta-analyses on the subject [1, 28, 29]. Nevertheless, longer stent patency may be important to maintain quality of life during the survival period post SEMS’ placement for patients with malignant distal CBD obstruction and to reduce the need for reintervention or the potential for cholangitis since the expected patient life span is increasing due to the development of palliative treatments, including chemotherapy, immunotherapy, and radiotherapy. Recently, the impact of biliary-stent-related adverse events during palliative chemotherapy has been emphasized from the perspective of patient morbidity [30].

Research trends show that physicians are mainly focused on the mechanical aspects of SEMS to increase patency, and the structure and composition of these stents are constantly evolving [31–34]. Despite this, the need for improved stent patency has not been met because of the lack of research on chemical prophylaxis for stent patency. Based on the study of Jang et al. [11], we will investigate whether aspirin use after index ERBD with SEMS for malignant distal CBD obstruction is effective and safe. Our study may provide further understanding of the potential role of aspirin in this patient population. If aspirin can help to maintain stent patency, patients will be able to keep their stents for longer periods of time alongside the very simple administration of one tablet a day, and this will reduce the need for reinterventions. Because aspirin is easily available, cheap, and safe with relatively few side effects, it can have a significant impact if it is found to be effective in this well-designed prospective study.

For this study, we have chosen to use aspirin as a chemoprophylactic agent to improve stent patency for several reasons. First, aspirin is considered to be very safe because it has been used by countless patients for a long time, and its efficacy, mechanism of action, and side effects have been studied comprehensively. Even though, there has been debate as to whether it actually reduces gastric-mucosal damage. Second, the anti-inflammatory effects of aspirin that inhibit the formation of prostaglandin by COX-2 inhibition seem to reduce the tissue inflammation induced by SEMS. Third, the use of aspirin may inhibit both mucin formation in the gallbladder, which is associated with biliary stone formation, and the coating with mucinous bile of the stent that may affect stent patency [14–17]. Nevertheless, the results of some studies have shown that the effects of aspirin are unclear. Last, the researchers of several basic and clinical studies have suggested that aspirin has an anti-tumor effect, and some large epidemiological studies, clinical studies, and meta-analyses have indicated that aspirin may have a significant effect on the prevention and treatment of cancer, especially colon cancer [35–40]. Several basic studies at various molecular genetic levels have provided an explanation for the anti-tumor effect of aspirin. It is known that aspirin leads to cell apoptosis by inhibiting Bcl-2 expression and downregulating COX-2 expression, which is known to convert arachidonic acid to prostaglandins, and it may reduce tumor-cell invasion through the downregulation of MMP-2 expression [41, 42]. Some studies have also provided evidence that aspirin promotes deoxyribonucleic acid (DNA) self-healing by the upregulation of hMLH1, hMSH2, hMSH6, hPMS2 [43], and XRCC expression [44], slowing down gene-mutation accumulation, and protecting normal cell DNA [32, 45]. Recent studies have suggested several new aspirin pathways, such as inhibiting the synthesis of prostaglandin E2 (PGE2) [46], controlling the number of circulating platelets and their activity levels to evade several innate anti-tumor effects [47–50], increasing chemo-agent toxicity, and downregulating cellular drug resistance [51, 52]. Since the results of these basic studies have mostly been conducted in vitro and have not been proven in humans, these outcomes cannot be presented as definitive mechanisms of aspirin’s effects.

This study will have some limitations. First, the patients will have malignant obstruction from various types of malignancies, and they may be receiving different kinds of treatments. This may affect SEMS’ patency. To mitigate this, we will conduct a subgroup analysis of the effects of the different treatments and cancers rather than control such factors because it is our opinion that aspirin could be effective even when prescribed in a variety of clinical situations. Second, we have had to make some assumptions in the calculation of the sample size. We calculated the sample size based on the most reasonable approach, but it is undeniable that this is a logical leap because stent patency has been reported very differently in diverse clinical situations.

The results of this study may provide a new evidence-based treatment option for patients with malignant distal CBD obstruction.

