### Randomization, blinding, and treatment allocation

The randomization lists will be generated using Random Allocation Software version 1.0.0 (free software developed by M. Saghaei, MD, Isfahan University of Medical Science, Isfahan, Iran) using the block randomization method developed by a research fellow at Seoul National University Hospital who is not involved in our trial. The patients who meet the selection criteria will be randomized at a 1:1 ratio in each group (test or control). As this is a double-blinded study, the researchers, patients, and other study personnel will be blinded to the treatment.

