### Interventions and management of the study drug

The enrolled patients will be randomly assigned to the test group or the control group. The drug administration will start within 30 days of successful placement of the index ERBD with a SEMS. The specifications of the stent (covered/partially covered/uncovered, caliber, length) were also decided by the physician’s discretion, taking into account the feature of obstruction site and the patient’s condition. And we allow the use of all biliary SEMS available in each institution regardless of manufacturers including the WallFlex biliary stent (Boston Scientific, Natick, MA, USA), the Bonastent (Standard SciTech Inc., Seoul, South Korea), the Niti-S biliary stent (Taewoong Medical Co., Ltd., Ilsan, South Korea), the Zilver biliary self-expanding stent (Wilson-Cook Medical Inc., Winston Salem, NC, USA), and the ARISTENT (CGbio Co., Ltd., Seongnam-si, South Korea), etc. Prophylactic rectally administered indomethacin or rectally administered diclofenac for post-procedural pancreatitis will not be used because none of the rectally administered non-steroidal anti-inflammatory drugs is commercially available in Korea. The patients in the test group will take one 100-mg enteric-coated aspirin tablet (Daewon Pharmaceutical Co., Ltd., Seoul, South Korea) per day before or after meals for 6 months, which was known to be physiologically equivalent to 75 mg plain aspirin [20]. And the patients in the control group will take one placebo tablet for 6 months. We planned a longer period of aspirin use for 6 months in comparison with the previous retrospective study [11] because the known median patency of SEMS in distal CBD obstruction was over 6 months [1, 5]. The patients will be followed-up in an outpatient clinic irrespective of whether the clinical outcomes, including stent malfunction, occur. Anti-cancer therapy, which is or will be received, will continue regardless of whether the patient is enrolled in the study.

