### Study outcome and assessment

The primary outcome of this study is the rate of stent dysfunction at 6 months. Stent dysfunction is defined as the presence of symptoms of obstructive jaundice or cholangitis in combination with confirmation of stent obstruction or migration via imaging (i.e., computed tomography and/or magnetic resonance imaging) after index SEMS’ insertion. Cholangitis will be diagnosed according to the Tokyo Guideline 2013 as follows: fever over 38 °C, evidence of an inflammatory response with an abnormal white blood cell level (< 4000/uL or > 10,000/uL) or a C-reactive protein level ≥ 1 mg/dL, jaundice (total bilirubin ≥2 mg/dL), abnormal liver function tests (alkaline phosphatase, gamma-glutamyl transferase, alanine transaminase, aspartate transaminase > 1.5 x standard deviation), and biliary dilatation at imaging tests [21]. The rate of stent dysfunction is defined as the percentage of patients who develop stent dysfunction during the follow-up period.

The secondary outcomes of this study are the duration of stent patency, the rate of reintervention, and any adverse events related to aspirin administration. The duration of stent patency will be evaluated on a day-scale as the duration between the index SEMS’ placement and the occurrence of stent dysfunction, or death in the case of patients without stent dysfunction. The rate of reintervention is defined as the percentage of patients who underwent an additional intervention for biliary drainage during the follow-up period after the index SEMS’ placement. For adverse events, a thorough investigation will be conducted to determine whether the adverse effects were related to aspirin administration.

Baseline characteristics and medical information of patients are also recorded in detail through the case report form including information as follows for further analysis: etiology, stage of disease, histologic feature, Charlson’s comorbidity index, history of hypertension, diabetes mellitus, pulmonary tuberculosis, cerebrovascular disease, coronary artery disease, liver or bile duct disease, peptic ulcer disease, any bleeding event, drugs in current use, smoking, alcohol use, family history, prior management including sphincterotomy, whether any biliary stent, further management including detailed information of chemotherapy, radiotherapy, surgery.

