### Data analysis

Blinding will remain in place until the statistician codes the statistical analyses of the primary and secondary outcomes. The statistical analyses will be done using the full analysis set according to the intention-to-treat principle, meaning that all the randomized patients will be analyzed in their allocated groups regardless of any protocol violations or early treatment discontinuations. We will also evaluate the outcomes through a per-protocol analysis set that will consider only the subjects who followed the protocol effectively. No formal interim analysis is planned.

We will compare the rate of stent dysfunction using Pearson’s chi-squared test with Fisher’s exact test and calculate the odds ratio of the event. The secondary outcomes (i.e., the duration of stent patency, the rate of reintervention, and the adverse events related to aspirin administration) will be analyzed using Pearson’s chi-squared test with Fisher’s exact test, Student’s *t* test and Kaplan-Meier curves, stratified by drug, and the hazard ratios between two groups measured using the Cox proportional hazards regression. We also plan to identify the further affecting factors for stent dysfunction by univariate and multivariate logistic regression analysis.

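### Cancer type and treatment are met by subgroup analysis only; the unadjusted primary comparison is valid but leaves a modest gain in precision unused

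*Protocol article*

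**What the plan says.** Among its limitations, the Discussion of the protocol article notes that patients will have different malignancies and different treatments, and says of this: "This may affect SEMS’ patency". The mitigation offered is: "we will conduct a subgroup analysis of the effects of the different treatments and cancers rather than control such factors". The reason given is the authors' view that aspirin may work across varied clinical settings.

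The Data analysis section fixes the primary comparison: "We will compare the rate of stent dysfunction using Pearson’s chi-squared test with Fisher’s exact test and calculate the odds ratio of the event". Covariates enter elsewhere: "We also plan to identify the further affecting factors for stent dysfunction by univariate and multivariate logistic regression analysis".

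Two further places matter. Under Interventions and management of the study drug, stent type is left open: "The specifications of the stent (covered/partially covered/uncovered, caliber, length) were also decided by the physician’s discretion". Under Study outcome and assessment, the case report form captures, among other items, "etiology, stage of disease, histologic feature", together with prior and later treatment.

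**The concern.** The plan names a prognostic problem and answers it with a tool for a different question. Factors that influence patency add variation to the overall comparison and can fall unevenly between the arms by chance. A subgroup analysis asks whether the aspirin effect differs across cancers or treatments. It leaves the overall estimate as noisy as before, and each subgroup has far fewer events than the trial.

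Adjusting the primary estimate for factors fixed before randomisation addresses imbalance and precision directly. The planned logistic model does not do this, because its stated purpose is to find factors associated with dysfunction. At stake is some precision, and protection against a post hoc argument if the arms differ on factors that the authors themselves regard as influential.

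**Working it through.** **1. Reproduce the plan's sample size.** Inputs from the Sample size section: 40% dysfunction at 6 months, 20% in the other arm, two-sided 5%, 80% power, 10% dropout. The text attaches the 20% to the non-aspirin group; the stated number is reproduced only if 20% is read as the aspirin rate, and that reading is assumed here.

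n per group = [1.960 × √(2 × 0.30 × 0.70) + 0.842 × √(0.40 × 0.60 + 0.20 × 0.80)]² / 0.20² = 81.2, so 82.

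Dropout: 82 / 0.9 = 91.1, so 92 per group and 184 in total. Both match the article.

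Power at 82 per group = Φ[(0.20 − 1.960 × √(0.42/82)) / √(0.40/82)] = 80.4%. With all 92 per group it is 84.7%. The unadjusted test is therefore the one for which the trial was sized.

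**2. What subgroups can show.** The same formula for 40% v 20% gives 51% power in a subgroup of half the trial (41 per arm) and 36% in one of a third (27 per arm). Interaction tests would be weaker still.

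**3. Size of chance imbalance.** Assume a factor present in 50% of patients, 82 per arm and simple 1:1 allocation. The standard deviation of the difference in prevalence is √(2 × 0.25/82) = 0.078, so a difference of 10 points or more has a probability of about 20%. Taking control-arm risks, such a difference shifts the unadjusted risk difference by about 1.6 points if the factor has an odds ratio of 2, 2.6 points at 3 and 3.6 points at 5. The design effect is 20 points.

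**4. What adjustment gains.** The article gives no prognostic strength, so a range is assumed. Simulated trials with 82 per arm and 40% v 20% compare the chi-squared test with a logistic model containing three binary baseline factors:

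| Odds ratio of each factor | Unadjusted power | Adjusted power | Change |
|---|---|---|---|
| 1 (not prognostic) | 81.0% | 81.0% | 0 |
| 2 | 80.6% | 82.5% | +1.9 |
| 3 | 80.3% | 85.1% | +4.8 |

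A longer list (four centres, four cancer types, stent covering and therapy; 8 parameters) was simulated at 40% v 22.1%. The 22.1% is the article's hazard ratio of 0.49 applied to 40%: 1 − 0.6^0.49. Unadjusted v adjusted power was:
- no prognostic value: 70.6 v 69.0%
- three factors at odds ratio 1.5 each: 70.4 v 70.9%
- three factors at odds ratio 2 each: 70.6 v 72.8%
- three factors at odds ratio 3 each: 69.8 v 76.3%

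A repeat with exactly three binary factors at both pairs of rates gave losses below 1 point when none was prognostic, gains of about 2 points at odds ratio 2, and gains of 5.0 and 6.6 points at odds ratio 3. A single binary factor gained about 0 to 1 point up to odds ratio 2, about 2 points at 3 and 4 to 5 points at 5.

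**5. How many covariates the data can carry.** Expected events run from 82 × (0.40 + 0.20) = 49 to 92 × (0.40 + 0.221) = 57. Eight parameters would leave about 6 to 7 events each, so the list has to be short.

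**The case against.** The strongest reply is that nothing here is wrong. Under 1:1 randomisation the unadjusted test is valid, chance imbalance is already allowed for in its type I error, and it is the test behind the 82 per group. This stands. A reader might infer that the primary result will be biased, and the article does not support that.

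The phrase about not controlling factors may also mean control by design, that is, not restricting cancers or treatments; the pragmatic reason given fits that reading better. This too stands, so the sentence should not be taken as a refusal of covariate adjustment. The evidence for an unadjusted primary comparison is the Data analysis section, which says so under either reading.

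A reader might go further in three ways:
- **The trial is already underpowered.** On the rates that generate its sample size it has 80.4% power. A figure near 70% appears only if the hazard ratio of 0.49 is applied to 40%, which is a separate question about the Sample size section.
- **Adjustment is free.** It costs a little if the factors are not prognostic, gains little if they are weak, and does not restore 80% on the hazard-ratio reading in any setting examined.
- **The allocation is unstratified.** The article describes block randomisation without naming strata, but a condensed article commonly leaves this to the full protocol, so nothing follows from it.

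Finally, the article's anti-cancer treatment includes therapy begun after enrolment, which cannot be used for adjustment. Only part of the heterogeneity can be dealt with in this way.

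**Conclusion.** The point holds as a worthwhile, inexpensive improvement. The plan identifies prognostic variation and mitigates it only by subgroup analysis, which addresses differences in effect and not imbalance or precision. The primary comparison remains valid, correctly sized on 40% v 20%, and unbiased by design.

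For a short list the expected change in power lies between a loss of at most about 1 point and a gain of 5 to 7 points. The upper end requires three factors that each have an odds ratio of about 3. These strengths, the 50% prevalences and the binary coding are assumptions; the article offers no figure for any of them.

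**What to change.** In the Data analysis section, before unblinding, pre-specify a primary estimate of the aspirin effect adjusted for:
- cancer type, in a few categories;
- anti-cancer therapy under way at randomisation, excluding therapy started later;
- stent covering (covered or partially covered v uncovered), if it is recorded.

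Use logistic regression standardised to a risk difference, so that the result is a marginal effect and not a conditional odds ratio. Keep the unadjusted chi-squared test as supportive. Report the cancer and treatment subgroups with interaction tests and label them exploratory. In the Discussion, say that subgroup analysis examines whether the effect varies, and point to the adjusted estimate as the response to prognostic variation.

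The cost is mainly wording. Cancer etiology is already recorded. Stent covering is known before randomisation because the stent is already in place, but the article's list of recorded items does not name it, so the case report form should be checked. Treatment dates are also needed, to separate therapy already under way from later therapy. The list must be fixed in advance and kept short, with about 50 to 57 events expected, and a very small loss of power is accepted if the factors prove not to be prognostic.

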## Trial status

This study is approved as protocol version 1.2 at the Seoul National University Hospital on 4 September 2017. The trial is currently in the recruitment phase. Study enrollment began on 12 October 2017. It is estimated that recruitment will be completed by 12 September 2019, with a study completion date of 5 September 2020.

## Data Availability

The datasets generated and/or analyzed during the current study will available from the corresponding author on reasonable request. In addition, following the completion of the study, the authors plan to make data available via publication.

## Abbreviations

AIMS: Aspirin for metal stents in malignant distal common bile duct obstruction
CBD: Common bile duct
ERBD: Endoscopic retrograde biliary drainage
ICH-GCP: International Conference on Harmonization and World Health Organization Good Clinical Practice
SEMS: Self-expandable metal stents
UDCA: Ursodeoxycholic acid
